## Abstract

**Background:**

Alcohol dependence affects approximately 3% of the English population, and accounts for significant medical and psychiatric morbidity. Only 5.6% of alcohol-dependent individuals ever access specialist treatment and only a small percentage ever seek treatment. As people who are alcohol dependent are more likely to have experienced health problems leading to frequent attendance at acute hospitals it would seem both sensible and practical to ensure that this setting is utilised as a major access point for treatment, and to test the effectiveness of these treatments.

**Methods/Design:**

This is a randomised controlled trial with a primary hypothesis that extended brief interventions (EBI) delivered to alcohol-dependent patients in a hospital setting by an Alcohol Specialist Nurse (ASN) will be effective when compared to usual care in reducing overall alcohol consumption and improving on the standard measures of alcohol dependence. Consecutive patients will be screened for alcohol misuse in the Emergency Department (ED) of a district general hospital. On identification of an alcohol-related problem, following informed written consent, we aim to randomize 130 patients per group. The ASN will discharge to usual clinical care all control group patients, and plan a programme of EBI for treatment group patients. Follow-up interview will be undertaken by a researcher blinded to the intervention at 12 and 24 weeks. The primary outcome measure is level of alcohol dependence as determined by the Severity of Alcohol Dependence Questionnaire (SADQ) score. Secondary outcome measures include; Alcohol Use Disorders Identification Test (AUDIT) score, quantity and frequency of alcohol consumption, health-related quality of life measures, service utilisation, and patient experience. The trial will also allow an assessment of the cost-effectiveness of EBI in an acute hospital setting. In addition, patient experience will be assessed using qualitative methods.

**Discussion:**

This paper presents a protocol for a RCT of EBI delivered to alcohol dependent patients by an ASN within an ED. Importantly; the trial will also seek to understand patients' perceptions and experiences of being part of a RCT and of receiving this form of intervention.

**Trial registration number:**

ISRCTN: ISRCTN78062794

## Background

### Scale of alcohol dependence in acute hospitals

A wide range of harms can ensue from risky drinking behaviour [1] many of which have to be dealt with by general hospitals on a daily basis. Alcohol is a factor in over 40 medical conditions that can lead to hospitalisation, which in 2010/11 accounted for 1.1 million hospital admissions in England, an increase of 12% compared with 2008/09 [2,3]. This figure does not include the 12% of ED attendances that are attributed to alcohol, which increases to 70% at peak times [4]. Additionally, prevalence of alcohol dependence in medical inpatients ranges from 3% to 47% [5,6]. Furthermore, over the past two decades, alcohol-related death rates have doubled [7]. The resulting annual cost to the UK NHS has been estimated at between £2 and £3 billion [8,9]. A rigorous assessment of alcohol-related harm showed that 38% of men and 16% of women (aged 16-64 years) have an alcohol use disorder, equating to approximately to 8.2 million people in England [10]. Of most concern is the estimate that 3-5% of the population in England (1.1 million people) are dependent on alcohol. However, treatment in acute settings would seem to be woefully inadequate, as in most cases alcohol dependent hospitalised patients are given pharmacological detoxification and, when stable, discharged into primary care without further treatment or support. This is a missed opportunity on several levels: early identification and treatment can reduce subsequent individual harm, and may prevent desease pregression, which will ultimatly reduce the overall burden of alcohol to society as a whole and the NHS in particular.

### Evidence for effectiveness of treatment in acute care settings

When considering brief intervention (BI) as a treatment approach for alcohol dependence in an acute care setting, it is important to note that the intensity of intervention does not seem to be a predictor of treatment effectiveness [11-15]. For that reason, brief treatments may be as effective as more intensive treatments in some patient groups. It is therefore noteworthy that, for those patients who are dependent on alcohol, treatments that are brief, timely and pragmatic have received little research focus. Furthermore, the assessment of the effectiveness of treatment is complex; particularly since between 12 to 35% of patients recover with little or no specialist intervention, a phenomenon described as "natural recovery" [16-19]. It has also been established that irrespective of their similarities and differences treatments seem to perform equally well, or badly [20,21].

It is well established that brief treatments are effective for hazardous and harmful drinkers [22] but may also have some efficacy in alcohol-dependent patients [22-30]. However, BI as a treatment option in acute hospitals has yet to be systematically tested in dependent drinkers [31-34]. The ED has been shown to be an appropriate setting in which to identify non-treatment seeking hazardous and harmful drinkers [31,35], and is potentially best placed to deliver effective care based on a BI approach [22,23,25-29,35,36]. However, to date, there has been little focus on the effectiveness of BI in alcohol dependence. A pragmatic non-randomised controlled study (Quaisi-experimental) of BIs by ASNs showed that 30% of alcohol-dependent patients' maintained abstinence for 6 months post treatment [37]. A subsequent study showed that patients treated by the ASN had significantly shorter stay in hospital and a significant reduction in alcohol consumption and dependence at 6 months [38]. Furthermore, a recent retrospective evaluation found that alcohol dependent patients realised as much benefit as non-dependent patients from BIs delivered by an ASN in acute care [35].

Given the scale of the problem, and the lack of choice currently available for this group of patients, it is vital to develop novel models of care which focus on the delivery of effective treatments in the acute care setting where this patient group most frequently presents. Indeed, Saitz proposed that enhanced brief intervention strategies may be effective in decreasing the direct complications associated with unhealthy alcohol use [11,39].

## Methods/Design

### Hypothesis

EBIs delivered to alcohol-dependent patients in a hospital setting by an ASN will be effective when compared to usual care in reducing overall alcohol consumption and improving on the standard measures of alcohol dependence.

### Overall aim of the study

To test the clinical and cost effectiveness of extended BI for individuals with alcohol dependence in an acute hospital setting.

The study objectives are:

1. To determine whether BI reduces overall alcohol consumption.

2. To determine whether BI is effective in the treatment of alcohol dependence.

3. To determine whether BI reduces the length of stay in hospital

4. To determine how patients feel about being approached in an opportunistic manner for screening for alcohol-related problems and subsequently being asked to be part of a research trial.

5. To determine the cost effectiveness of BI for alcohol dependence

The study is a randomized controlled trial. The study has been approved by North West Research Ethics Committee ref: 09/H1005/61, and is fully compliant with the Helsinki declaration 2008.

### Setting

The trial will be conducted within an acute NHS Hospital Trust with an ED based within the North West region of England. In order to minimise the risk of contamination from other alcohol interventions, the setting currently has no protocols for screening or advice within their ED or hospital wards.

### Design

The trial comprises three parts: the first is a test of the clinical effectiveness of the EBI, the second is an assessment of the patient's experience of the intervention using qualitative methods, while the third is an assessment of cost effectiveness of the BI.

### Blinding

The nature of delivery of EBI precludes blinding of subjects. However, the nurses conducting the follow-up assessments at 12 weeks and 6 months remain blinded to treatment allocation. The statistician involved in data analyses will be blinded for treatment allocation.

### Trial inclusion and exclusion criteria

Trial inclusion and exclusion criteria have been selected to ensure that patients are able to understand the importance of adherence to the trial protocols, and are able to provide contact details for follow-up. It is also important to ensure that patients' medical co-morbidity will not necessitate long term hospitalisation, as this will prevent the delivery of EBI as an out-patient. Furthermore, to prevent contamination by other treatments the patient must not have been involved in any alcohol-specific treatment for alcohol dependence in the previous 6 months.

All ED attendees over the age of 17 years, with a score equal to or greater than 16 on the AUDIT screening tool, who live within the local area and are amenable to attend follow-up clinics for interventions, are eligible.

### Trial Recruitment Process (See flow diagram Figure 1)

**Figure 1 F1:**
[figure not shown]
**Trial Recruitment Process**.

Clinicians performing treatment or triage within the ED will utilise their clinical examination to determine the likelihood of the admission being alcohol-related. On identification or suspicion of an alcohol-related problem, the clinician will refer to the ASN for further assessment. The ASN will also visit the ED and Medical Assessment Unit daily to identify cases. The ASN will then screen all patients using the AUDIT screening tool. An AUDIT score of 16 and above will be considered a positive screen. Patients will then be assessed against inclusion/exclusion criteria.

### Trial consent procedure

All eligible patients will be given relevant verbal and written information about the research and asked to consent. Due to the opportunistic nature and design of the study, patients will be asked to provide written consent on initial assessment. This is to ensure that the population recruited is representative of the clinical population attending ED whether aware or unaware of the role of alcohol in their presentation. Patients will be able to withdraw from the study at any point. If reasons for opting out are volunteered by the patient, we will ask consent to use this information. The ASN will be the nurse taking consent from the patient and will discuss with the patient's named nurse if they agree that the patient is physically and mentally fit to give consent to the study. The patient will be provided with a patient information leaflet (PIL) which the nurse will discuss in detail. If the patient gives consent, they will undergo a comprehensive assessment at which the ASN will collect all baseline demographic data, information on co-morbidity, complete all screening tools, and take a full alcohol history. Those patients unwilling to consent to randomisation will be given usual clinical care, and be asked to consider consent for their demographic data to be collected, and will be asked if they wish to take part in the qualitative part of the study. A separate PIL will be used for the qualitative analysis, who will then be interviewed by the qualitative researcher (QR).

### Trial randomization procedure

Following consent, the research nurse will complete the screening and diagnostic tools:

a) Severity of Alcohol Dependence Questionnaire (SADQ),

b) Leeds Dependency Questionnaire (LDQ),

c) Readiness to Change Questionnaire (RCQ), and

d) EuroQoL EQ-5D.

The patient will then be randomized to either the intervention or control group by the research nurse. Patients will be randomized using sequentially numbered opaque sealed envelopes prepared according to a computer-generated randomisation allocation sequence. Block randomisation using randomly varying block sizes (prepared using Stata version 8.2) will ensure equal numbers of patients are recruited into each group. Randomisation services will be provided by an independent statistician at the Clinical Trials Research Centre, University of Liverpool.

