### Control group

The control group will receive the same assessments as the intervention group but they will not receive the EBI. They will receive normal clinical care, which may or may not include referral to a specialist alcohol service. Follow up visits will be arranged 12 weeks and 6 months following recruitment into the study, either in outpatients, at home or by telephone by a nurse researcher blinded to treatment group.

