### Follow Up Strategy

This population can be difficult to follow-up and loss to follow-up in this setting has been reported as high as 48% [38]. Therefore, the research nurse will take an address and telephone details for the patient or relative/carer. The patient will also be asked to give permission for the research team to contact their General Practitioner (GP) to obtain additional data. To facilitate ease of access for treatment and follow-up, patients will be offered a range of follow-up options either in the hospital, on the telephone, or at home. Two weeks prior to the follow-up appointment, the patient or other named contact will be contacted to determine if they will be attending their appointment. The day before their appointment, patients will be contacted to remind them that their follow-up appointment is due the next day. If the patient is unable to be contacted, they will be sent a letter asking them to contact the team in order to arrange follow-up. If the patient is unable to be contacted via telephone or fails to respond to a letter for the 6 month follow-up appointment, the research nurse will visit the patients home to determine a) if the patient still resides at that address, and b) if the patient is still willing to undertake a follow-up appointment. If the patient cannot be contacted by the team at this stage, they will be said to be lost to follow-up.

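### The role that randomises patients also makes the last-resort 6-month home visit, so the promised blinding of follow-up is not secured

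*Protocol article*

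**What the plan says.** All references are to the protocol article.

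- **Baseline and allocation.** Trial randomization procedure: "Following consent, the research nurse will complete the screening and diagnostic tools", a list that includes the SADQ. It continues: "The patient will then be randomized to either the intervention or control group by the research nurse". The mechanism is given as: "Patients will be randomized using sequentially numbered opaque sealed envelopes prepared according to a computer-generated randomisation allocation sequence".
- **Baseline again, with another role.** Trial consent procedure: "the ASN will collect all baseline demographic data, information on co-morbidity, complete all screening tools, and take a full alcohol history". The ASN is the alcohol specialist nurse, who also delivers the extended brief intervention (EBI; Part A-Treatment group).
- **Blinding.** Blinding: "the nurses conducting the follow-up assessments at 12 weeks and 6 months remain blinded to treatment allocation". Control group: follow-up is done "by a nurse researcher blinded to treatment group". The Abstract and Part A-Treatment group make the same promise, for a researcher and for an assessor respectively.
- **Tracing.** In Follow Up Strategy the research nurse takes contact details. If telephone or letter fails at 6 months, "the research nurse will visit the patients home to determine a) if the patient still resides at that address" and whether he or she will still attend. A patient who cannot be reached at that stage is classed as lost.

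**The concern.** Patients cannot be blinded, and the primary outcome is a questionnaire score at 6 months. Protection against bias at follow-up therefore rests on staff who do not know the arm. That protection has two parts: how the outcome is recorded, and who gets recorded at all.

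The article covers the first part by promising blinded assessors. It does not cover the second. The home visit is the last step before a patient is counted as lost, and it goes to the role title that performed the randomisation. A nurse who knows the arm could, without meaning to, persist longer or persuade harder in one group. With half the patients expected to be missing, the set of patients analysed could then differ between arms in a way that is linked to outcome.

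**Working it through.** No figure in the plan needs reproducing for the point about roles. The check is a comparison of who does what, followed by simple arithmetic on planned loss.

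**Roles side by side**

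| Task | Role named | Section | Aware of arm? |
|---|---|---|---|
| Baseline tools | ASN | Trial consent procedure | Yes, later, as therapist |
| Baseline tools including SADQ | Research nurse | Trial randomization procedure | Not yet |
| Randomisation | Research nurse | Trial randomization procedure | Yes, by inference |
| EBI sessions | ASN | Part A-Treatment group | Yes |
| Taking contact details | Research nurse | Follow Up Strategy | Timing not stated |
| Reminders and letters | No role named | Follow Up Strategy | Not stated |
| Last-resort 6-month home visit | Research nurse | Follow Up Strategy | Yes, if the role is the same |
| 12-week and 6-month assessment | Nurses, assessor, nurse researcher or researcher | Blinding; Part A; Control group; Abstract | Promised no |

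**Step 1: does the randomising role know the arm?** The text does not say in words who opens the envelope. It says that the research nurse randomises and that sealed envelopes are used. It is a fair inference that this nurse sees the result.

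**Step 2: does the conflict between the two baseline sections offer a way out?** No. If the research nurse and the ASN are the same person, the home visitor is the therapist. If they are different, the home visitor holds the role that randomised. On either reading, the role named for the home visit knows the allocation.

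**Step 3: are the labels separated?** The research nurse (randomisation, home visit) and the blinded nurse researcher (Control group) have nearly identical names. No sentence says that different people hold them.

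**Step 4: how much room is there for selective retention?** From Sample Size calculation:

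- First calculation: 130 per group, 50% dropout. 130 × (1 − 0.50) = 65 per group evaluable, so 2 × 130 − 2 × 65 = 130 of 260 patients are expected to be missing.
- Revised calculation: 206 recruited, 103 required. 206 − 103 = 103 of 206 are expected to be missing.

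The document does not say how many patients would reach the home-visit stage, so the exposed share cannot be computed.

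**Step 5: would the primary analysis absorb it?** Analysis of primary outcomes specifies ANCOVA on 6-month SADQ, controlling for baseline and without adjusting for missing data. Controlling for baseline deals with loss that depends only on arm and baseline SADQ, provided the model is right. It does not deal with effort that differs by arm and brings in patients whose 6-month scores differ from those of missing patients with the same baseline.

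**The case against.** The strongest reply is that the blinding promise is explicit and repeated. Four sections give the follow-up assessment to blinded staff, and a nurse who randomised a patient could not remain blinded to that patient, so a different assessor is already implied. Follow Up Strategy names the research nurse only for contact details and the home visit. That visit checks residence and willingness; collecting the SADQ is not mentioned. A shared job title does not show that one individual does both tasks. Staff delegation is also the kind of detail that an article leaves to the full protocol. Finally, sensitivity analyses for missing data are planned.

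Much of this stands. A reader might infer that an unblinded nurse collects the 6-month SADQ and that the protocol therefore contradicts its own blinding statement. The document does not support that: no section gives outcome collection to anyone who knows the arm, and the sections can be honoured if different people fill the roles.

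The reply does not remove the retention problem. The article is not silent about the home visit: it assigns that task, and it assigns it to the role that randomises. Even if every assessment is blinded, the step before it need not be. The sensitivity analyses may show how much missing data matter, but they do not prevent selective follow-up or alter the primary estimate.

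**Conclusion.** The point holds as a weakness in how follow-up tasks are allocated, not as a direct contradiction. As written, a role that knows the allocation takes part in deciding who is followed up for the primary endpoint, and nothing in the article separates that role from the blinded follow-up nurse. The disagreement over who completes the baseline tools adds to the uncertainty.

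This rests on two assumptions: that the nurse who randomises sees the envelope's contents, and that the same title in two sections means the same role. Both are natural readings, and neither is stated.

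The direction and size of any bias are unknown. A reader might want to express it as an inflated type I error by assuming a shift in the interviewer's scoring. That would treat every 6-month SADQ as taken by an unblinded interviewer, which the plan excludes, and would need an SADQ standard deviation that the document does not give. The document supports only that the room for selective retention is large, with half the sample planned as lost, and that the primary analysis does not correct for it. This should be changed, but it does not undermine the design as a whole.

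**What to change.** 1. In Blinding and Follow Up Strategy, state that staff who randomise patients or deliver EBI do not make reminders, tracing contacts, home visits, or the 12-week and 6-month assessments. Give these tasks to the blinded follow-up nurses already in the trial.
2. Use distinct role names throughout, for example *randomising nurse* and *blinded follow-up nurse*, in place of research nurse and nurse researcher.
3. Reconcile Trial consent procedure with Trial randomization procedure on who completes the baseline tools.

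The envelopes should not be moved to the ASN as a way of keeping the research nurse blinded. The ASN identifies and screens cases, takes consent and treats, so holding the envelopes as well would weaken allocation concealment.

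The cost is a few sentences and some reallocation of nurse tasks. No change to sample size, endpoint or analysis is needed.

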### Data collection/management process

#### **Intervention**

All data will be collected prospectivley utilising a Case Report Form (CRF). Data will be collected at baseline and each follow-up point. Data from the CRF which will carry only an anonymised number will be entered directly on a MACRO™ electronic database system. Patient information will be kept on a patient log, which will remain in a locked filing cabinet in a clinical room at the clinical site, alongside the anonymised case report files.

#### **Qualitative**

Interviews will be digitally recorded, anonymised and transcribed by a third party. All digital files will be destroyed within 12 weeks of interview. NVivo, computer assisted qualitative data analysis software that stores and retrieves data will be used.

#### **Economic**

For retreval of hospital utilisation data, researchers will use hospital based electronic recording systems. For GP data, the researchers will visit individual patient GP surgeries and collect data from case files and electronic systems. Ambulance data will be collected electronically. All data will be entered onto the CRF, and will be entered directly in to a MACRO™ electronic database system.

